**Figure 1 F1:**
[figure not shown]
Project overview.

### Data collection and monitoring

2.10

Pre-clinical research training: All personnel in clinical research will be relatively fixed and receive unified training before the start of clinical trial, so that all researchers have a better understanding of the clinical trial plan.Data collection: Two inspectors will be appointed to oversee and inspect the research process. The data will be collected by the designated person. To ensure the accuracy of the data, two investigators will enter and proofread the data respectively. All cases will be completed in accordance with the design requirements of the Case Record Form. Withdrawal from the study and loss of follow-up (and the causes) will be fully documented.Quality control: The project leader supervises and checks the progress of the research, and checks whether the records and reports of the research data are true, accurate and complete. And the completed “Research Cases” for timely monitoring. All acupuncture and moxibustion operations will be carried out by specialized chief physicians to ensure the accuracy of acupuncture and moxibustion sites.

### Statistical analysis

2.11

Statistical analysis includes statistical description and statistical inference. The statistical description of quantitative indicators includes mean, standard deviation, median, minimum and maximum. Qualitative indicators are described by frequency tables and component ratios.

All statistics will be analyzed by Statistical Packages of Social Sciences (SPSS) software (version 22.0). The continuous variables will be described using mean ± standard deviation. Continuous variables subject to normal distribution will be analyzed by Student *t* test. The Rank Sum test will be used for non-normal distribution data, ANOVA test will be used for comparison among three groups, wilcoxon test is used for non-normal distribution data. Enumeration datas will be expressed as rates, and the comparison of effective rates between groups are performed by X^2^ test. *P* < .05 will be considered statistically significant.

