### Sample size calculation

2.4

In this study, it is stipulated that only when the anterior ophthalmic process is reduced by ≥1 mm can be promoted. Exophthalmus references standard deviation is 1.3 mm, preliminary tests showed that Chinese herbal medicine could reduce the protrusion degree by 1.9 ± 1.1 mm,^[9,10]^ so we chose to reduce degree of exophthalmus to calculate the sample size, according to the α = 0.05, β = 0.1, σi is overall standard deviation for each group, μi means the population mean of each group is 1.3, K refers to the number of sample groups are 3, μ = Σμi/k, ψ of value through the check ψ of table that is 2.52, the formula for sample size = ψ2(Σσi2/k)/[Σ(μi−μ)2/(k−1)] calculated sample size is equal to about 36, considering a 10% loss to follow-up, determine the test each sample size for 40 cases, The total sample size is 120.

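### The observed distribution decides whether each primary outcome is compared by means or by ranks, so the primary test and estimand are not fixed in advance, although the trial was sized on a reduction in mm

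*Protocol article*

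**What the plan says.** Section 2.11 (Statistical analysis) ties the test to the shape of the data: "Continuous variables subject to normal distribution will be analyzed by Student" t test. The next sentence gives the alternative and the three-group version together: "The Rank Sum test will be used for non-normal distribution data, ANOVA test will be used for comparison among three groups, wilcoxon test is used" (the last again when data are not normal). The section does not say how normality is judged, or whether arms or residuals are checked.

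The descriptive plan in the same section carries no such condition: "The continuous variables will be described using mean ± standard deviation", and "The statistical description of quantitative indicators includes mean, standard deviation, median, minimum and maximum".

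Section 2.4 (Sample size calculation) builds the trial on millimetres: "so we chose to reduce degree of exophthalmus to calculate the sample size". It sets a benchmark ("only when the anterior ophthalmic process is reduced by ≥1 mm can be promoted") and a spread ("Exophthalmus references standard deviation is 1.3 mm"), and cites a preliminary reduction of 1.9 ± 1.1 mm.

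Section 2.7.1 names two primary outcomes, exophthalmos degree and the TCM syndrome score. It gives the instrument for the first but not its reading step, and does not say whether the level or the change in exophthalmos is compared.

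**The concern.** The rule in section 2.11 covers every continuous variable, so it covers both primary outcomes. A t test or ANOVA compares means in mm or points. A rank test compares orderings and says nothing directly about a 1 mm difference. Letting the trial's own data choose between them has three consequences:

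- The primary P value is not defined until the data have been looked at.
- Because no normality check is named, whoever runs the analysis has latitude over which branch applies.
- One primary outcome could be reported on means and the other on ranks.

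The gain is small. With 36 to 40 patients per arm, comparing means does not need normally distributed data. A normality test can also reject merely because readings are rounded.

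**Working it through.** **1. The protocol's own figure.** Two means, difference 1 mm, SD 1.3 mm, two-sided α = 0.05, power 90%: n = 2 × (1.960 + 1.282)² × 1.3² / 1² = 2 × 10.51 × 1.69 ≈ 35.5, so 36 per arm. With 10% loss, 36 / 0.90 = 40.

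The formula printed in section 2.4 also gives 36 if the arm means are assumed to be 1.9, 1.0 and 1.0 mm and the SDs 1.1, 1.3 and 1.3 mm: 2.52² × [(1.21 + 1.69 + 1.69)/3] / [(0.36 + 0.09 + 0.09)/2] = 6.35 × 1.53 / 0.27 = 36.0. Either way the size rests on means in mm.

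**2. How often the check would fail.** Inputs from the documents: 36 per arm, SDs of 1.1 and 1.3 mm. Assumptions: true changes are exactly normal; the change is analysed; baseline is normal with mean 20 and SD 2.5 mm; before and after readings are each rounded to the instrument's step; normality is checked by Shapiro-Wilk at 5% in each arm; one failing arm triggers the switch. The step is not stated, so a range is shown.

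| Reading step (assumed) | Arm with SD 1.1 fails | Arm with SD 1.3 fails | At least one of three arms fails |
|---|---|---|---|
| 1 mm | 93.0% | 73.2% | 1 − 0.070 × 0.268² = 99.5% |
| 0.5 mm | 18.7% | 13.1% | 1 − 0.813 × 0.869² = 38.6% |
| 0.1 mm | 5.2% | 5.0% | 1 − 0.948 × 0.950² = 14.4% |

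The last column combines one arm with SD 1.1 and two with SD 1.3. Direct simulation of the three arms gave 99.6%, 38% and 16%. Three independent checks of truly normal data give 1 − 0.95³ = 14.3%, so 0.1 mm is close to nominal.

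**3. Sensitivity to the other unstated choices.**
- Pooled residuals instead of separate arms: 71% at 1 mm and 12% at 0.5 mm.
- Lilliefors instead of Shapiro-Wilk, any arm: 100% at 1 mm and 77% at 0.5 mm.
- The level in whole mm instead of the change (assumed SD 2 to 3 mm): 11% to 26% per arm. With equal SDs this is 1 − 0.8925³ = 29% to 1 − 0.740³ = 60% for any arm.
- TCM score: the range is 0 to 3 × 6 + 3 × 3 + 1 + 1 = 29. Rounding normal changes to whole points gives about 7% to 11% rejection per arm at assumed SDs of 3 to 5 points.

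**4. What the switch does to the result.** Readings to 1 mm, 36 per arm, Kruskal-Wallis taken as the three-group rank test:
- Type I error of the data-driven rule: 4.6% (SD 1.3) to 5.4% (SD 1.1).
- Power at means 1.9/1.0/1.0, ANOVA against ranks: 92% and 91% (SD 1.1 in all arms); 82% and 80% (SD 1.3 in all arms).
- Disagreement on P < .05, readings to 1 or 0.5 mm: about 3% to 4% at means 1.9/1.0/1.0 and about 6.5% at 1.5/1.0/1.0.

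**The case against.** The best reply is that the rule does little harm and that the alarming figure depends on assumptions. Much of this stands.

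- **Reading step.** A reader might infer that exophthalmos will almost always fail the check. The documents do not support that. Whole-millimetre reading appears nowhere in them, nor does a formal 5% test, an any-arm trigger or the analysis of change. The 99% figure belongs to that one combination.
- **Loss of the mm result.** A reader might infer that the rank branch leaves no millimetre figure. It does not: section 2.11 describes continuous variables by mean ± SD whatever test is used, so arm means and their difference remain available. Neither branch promises a between-arm difference with a confidence interval, so the normality rule does not cause that absence.
- **Error rates.** A reader might infer inflated type I error or lost power. Step 4 shows neither to any material degree, and some disagreement between two valid tests is ordinary.
- **TCM score.** Rounding to whole points adds little rejection at plausible spreads, so the switch cannot be said to be likely for that outcome on this ground.
- **Wording.** The ANOVA clause carries no explicit normality condition. But it stands between two rank-test clauses for non-normal data, and the natural reading is that it gives way to the second.

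The reply does not remove the rule itself. This is not detail left to an unseen analysis plan: the article states how the test is chosen, and the choice depends on the data.

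**Conclusion.** The point holds as one of pre-specification. Section 2.11 leaves the primary test and estimand to the observed distribution, possibly differently for the two primary outcomes, while section 2.4 commits the trial to a reduction in mm. The rank branch would neither test nor estimate that quantity.

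How often the switch would occur cannot be fixed from the documents. Under the Shapiro-Wilk any-arm assumptions for change in exophthalmos it runs from near nominal at 0.1 mm, through about 38% at 0.5 mm, to about 99% at 1 mm. In about 3% to 6.5% of simulated trials the choice of test decides whether P < .05. These figures assume normal true changes, 36 per arm, and arm means and SDs only partly given in section 2.4. It is a cheap improvement to make, not a threat to the trial's validity.

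**What to change.** In section 2.11, remove the normality-dependent choice for the two primary outcomes. State one analysis for each in advance: a linear model of ANOVA type for the mean, with heteroscedasticity-robust standard errors if wanted, reported as between-arm differences in mm and in points with 95% confidence intervals. Keep the rank test as a labelled sensitivity analysis, reported whatever the distribution looks like.

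The cost is a few sentences. No patients, visits or special software are needed. The small downside is somewhat less robustness of the primary analysis to outliers, which the sensitivity analysis covers.

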### Study design

2.1

This is a prospective, randomized controlled clinical trial with three parallel arms. We will recruit 120 patients from The Longhua Hospital affiliated to Shanghai University of Chinese Medicine. All patients will be randomly assigned to the experimental group (Pingmu Decoction + acupuncture), control group 1 (Chinese medicine group) and control group 2 (acupuncture group). All patients will maintain basic treatment for thyroid-related eye disease: methimazole and levothyroxine sodium tablets (both from Merck & Co, LTD, Germany). Dosage will be adjusted every 28 days according to the patient's thyroid function level. Control group 1 (Chinese medicine group), Pingmu Decoction will be required to take orally twice a day, 1 bag each time., control group 2 (acupuncture group) will be treated with acupuncture alone. The experimental group was treated with pingmu Decoction combined with acupuncture. All treatments will be administered for 12 weeks.

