### Randomization and allocation

2.6

We will randomize all included patients using a table of random numbers. The 120 patients will be randomly divided into the experimental group, control group 1 and control group 2 in a 1:1:1ratio according to the treatment order.

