#### Primary outcomes

2.7.1

Exophthalmos degree. Measurement of prominence of the eyeball: Use the ocular protrusion measuring instrument (model YZ9) to measure the degree of exophthalmia(Which brand is called Crane and produced by Suzhou liuliu Vision Co., LTD.)TCM syndrome integral

According to the diagnostic criteria of Deficiency of Yang qi and blockage of phlegm and blood stasis formulated in 2002 edition of Clinical Research Guidelines for New Chinese Medicine.^[11]^ Main symptoms: fear of cold, lack of power, eyeball swelling pain; Secondary symptoms: tepid limbs, pale face, self - perspiration. The body of the tongue is fat or normal, the tongue is pale purple, or there are petechial spots, or the veins under the tongue are purple and angry. The tongue coating white greasy, pulse heavy fine astringent. According to the degree of occurrence of the main symptoms: no, mild, moderate and severe, they will be recorded as 0, 2, 4 and 6 points respectively, and according to the degree of occurrence of secondary symptoms: no, mild, moderate and severe, they will be recorded as 0, 1, 2 and 3 points respectively. The tongue image and pulse image of the block syndrome of phlegm and blood stasis will be scored 1 and 0 points according to whether they are consistent with deficiency of Yang qi and blockage of phlegm and blood stasis. TCM syndrome integrals will be recorded once before and after treatment in the three groups.

Efficacy of TCM symptoms will be determined by integral method: Efficacy index(n) = ((post-treatment score − pre-treatment score)/(pre-treatment score)) × 100%

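### Section 2.11 compares the arms with tests that do not adjust for baseline, and names Wilcoxon, a two-sample or paired test, as the non-normal counterpart of the three-group ANOVA

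*Protocol article*

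**What the plan says.** Section 2.1 sets out the design: "This is a prospective, randomized controlled clinical trial with three parallel arms". Section 2.6 allocates patients to the "experimental group, control group 1 and control group 2 in a 1:1:1ratio".

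Section 2.11 then names the tests for continuous outcomes:

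- "Continuous variables subject to normal distribution will be analyzed by Student"'s t test.
- "The Rank Sum test will be used for non-normal distribution data", with no number of groups given.
- "ANOVA test will be used for comparison among three groups, wilcoxon test is used for non-normal distribution data".
- A P value "< .05 will be considered statistically significant", with no adjustment for multiple comparisons named.

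Section 2.11 mentions no baseline covariate. It also does not say whether the tests apply to post-treatment values or to changes from baseline.

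Baseline values do exist. Section 2.7.1 states that "TCM syndrome integrals will be recorded once before and after treatment in the three groups", and its efficacy index is a percentage change from the pre-treatment score. Section 2.4 sizes the trial on the reduction in exophthalmos. Section 2.7.2 grades response by a decrease in protrusion of at least 1 mm or at least 2 mm. The last two are only possible if protrusion is measured before treatment.

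**The concern.** There are two separate weaknesses.

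First, the pre-treatment value is usually a strong predictor of the post-treatment value of the same measurement. A t test or one-way ANOVA cannot use it as a covariate. Subtracting it to form a change score uses it with a fixed slope of 1, whereas ANCOVA estimates the slope. With about 36 evaluable patients per arm, the unadjusted tests give wider intervals than the collected data allow. A change score also leaves a regression-to-the-mean remainder of any chance imbalance at baseline.

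Second, the sentence on three groups pairs ANOVA with Wilcoxon. Wilcoxon comes in a rank-sum form for two independent samples and a signed-rank form for paired data. Neither gives a single test of three arms. An analyst who reaches the non-normal branch must either substitute another test or run Wilcoxon on pairs of arms, and the plan has no rule for the latter. This branch may well be used, because the TCM score is a primary outcome built from graded items (0/2/4/6, 0/1/2/3 and 0/1) and may not look normal.

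**Working it through.** **Inputs from the article.** There are three arms, 1:1:1 (sections 2.1 and 2.6). The design error rates are "according to the α = 0.05, β = 0.1", the SD is 1.3 mm, the reduction regarded as worthwhile is 1 mm, the loss is 10%, and the size is about 36 per group raised to 40, or 120 in total (section 2.4). The analysis threshold is .05 (section 2.11).

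**Assumed inputs.** The article gives no correlation ρ between the baseline and week-12 values. I take ρ = 0.5 to 0.9 and equal SDs before and after treatment.

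**Step 1: the plan's own size.** A two-group comparison of means with difference 1 mm, SD 1.3 mm, two-sided α 0.05 and power 90% needs 2 × (1.960 + 1.282)² × 1.3² / 1² = 35.5, so 36 per group. Then 36 / 0.9 = 40, and 3 × 40 = 120. This reproduces the stated figures, although not through the formula that section 2.4 prints, which is a separate matter. I use 36 per group as the reference below.

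**Step 2: ANCOVA against the unadjusted analyses.** With common variance σ² before and after, the variance per patient is:

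- post-treatment value: σ²
- change score: 2(1−ρ)σ²
- ANCOVA: (1−ρ²)σ²

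Hence ANCOVA/change = (1−ρ²) / [2(1−ρ)] = (1+ρ)/2, and ANCOVA/post = 1−ρ².

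| ρ | ANCOVA / change | n matching 36 on change | ANCOVA / post | n matching 36 on post |
|---|---|---|---|---|
| 0.5 | 0.75 | 27 | 0.75 | 27 |
| 0.6 | 0.80 | 29 | 0.64 | 24 |
| 0.7 | 0.85 | 31 | 0.51 | 19 |
| 0.8 | 0.90 | 33 | 0.36 | 13 |
| 0.9 | 0.95 | 35 | 0.19 | 7 |

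Read the other way, 36 patients per arm analysed by ANCOVA are worth 36/0.80 = 45 on change scores at ρ = 0.6, 36/0.90 = 40 at ρ = 0.8 and 36/0.95 = 38 at ρ = 0.9.

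**Step 3: which comparison applies.** Sections 2.4, 2.7.1 and 2.7.2 all express effects as a reduction or a change, so the change-score columns are the likely ones. The post-value columns apply only if raw week-12 values are tested, which section 2.11 neither states nor excludes.

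**Step 4: rank tests on three arms.** In 10,000 simulated trials with no treatment effect (36 per arm, exponential data), Kruskal-Wallis at .05 rejected in 0.050 of trials. Three unadjusted pairwise Wilcoxon rank-sum tests gave at least one rejection in 0.119. The large-sample value for three pairwise normal comparisons is 0.122. If the three tests were independent it would be 1 − 0.95³ = 0.143, but they share arms.

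**Step 5: the two contrasts of interest.** Combination versus decoction and combination versus acupuncture share the combination arm, so with equal arms their test statistics have correlation 0.5. Two unadjusted tests at .05 then carry a familywise error of 0.091 (bivariate normal).

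**The case against.** **Baseline.** A reader might infer that the plan discards the baseline value. The documents do not support that. The sizing variable, the TCM efficacy index and the response categories are all relative to baseline, and section 2.11 does not fix the analysed variable. If change is analysed, baseline is used, and in a randomised comparison the result is unbiased. At ρ = 0.7 to 0.9 the saving from ANCOVA is only 15% to 5% of the sample. The large gains in the post-value columns cannot be presented as the expected loss.

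**An unseen analysis plan.** A covariate model could stand in a fuller document, and an article's silence on covariates would not by itself be a finding. This objection has force. However, section 2.11 does more than stay silent: it lists the tests, and none of them adjusts for baseline. Deferral to another document also does not repair a named test that does not fit three groups.

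**The Wilcoxon sentence.** The rank sum test named just before it might be meant generically, covering a three-sample version, with Wilcoxon kept for pairs or for before-after comparisons. That is possible, but the text does not say so. Both rank tests are assigned to non-normal data with nothing to separate them, and the clause as written sets Wilcoxon beside the three-group ANOVA. On either reading the wording needs correcting.

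**Familywise error.** A reader might infer that the plan prescribes three unadjusted pairwise Wilcoxon tests and so has a 12% error rate. Section 2.11 describes no such procedure. The 12% is what would follow if the gap were filled that way, and pairwise t tests would raise the same issue.

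**Choice of test by distribution.** Choosing a parametric or rank test by the distribution of the data is conventional. I attach no size to it.

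**Conclusion.** The point holds in two limited parts. The plan should change on both, but neither invalidates the trial.

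The firm part is that no test named in section 2.11 for a three-group comparison of non-normal data is identifiably able to make one. It matters only if that branch is used.

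The second part is lost precision. On the likely change-score analysis, ANCOVA has 75% to 95% of the variance, equivalent to 27 to 35 patients doing the work of 36 per arm. This rests on an assumed ρ of 0.5 to 0.9 and equal SDs before and after treatment. The article gives neither ρ nor the SD at both times, so the size cannot be fixed more closely. If raw post-treatment values were tested, the ratio would be 75% down to 19% over the same range.

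**What to change.** Reword section 2.11, and the analysis plan if there is one, as follows.

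1. Primary analysis for exophthalmos and for the TCM score: ANCOVA of the week-12 value on treatment group, with the baseline value of the same measure as covariate (general linear model in SPSS).
2. Report the two combination-versus-control differences with confidence intervals. Protect them either by requiring a significant global three-group test first or by a Holm or Dunnett-type adjustment. Changing to ANCOVA alone would leave the 9% of Step 5.
3. If a rank analysis is kept, name Kruskal-Wallis for the three-group comparison. Limit Wilcoxon to adjusted pairwise follow-up (rank-sum) or before-after comparison within an arm (signed-rank), and say which form is meant.

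The cost is a wording change. The baseline values are already collected, SPSS runs all of these analyses, and no patients, visits or clinical procedures change.

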**Methods/Design::**

A prospective, randomized controlled clinical trial will be conducted to evaluate the efficacy and safety of Pingmu Decoction combined with acupuncture in the treatment of non-active thyroid-related eye disease in patients with Yang qi deficiency and phlegm-blood stasis syndrome. A total of 120 patients with non-active thyroid-related eye disease, namely deficiency of Yang qi and blockage of phlegm and blood stasis, are randomly divided into 3 groups and treated for 12 weeks. All three groups will maintain basic western medicine treatment. The primary outcomes are to observe the degree of prominence of eyes, and the TCM syndrome scores. The secondary result is clinical efficacy. Free triiodothyronine (FT3), free thyroxine (FT4), thyroid stimulating hormone (TSH), and thyroid stimulating hormone receptor antibody (TRAb)will be used as the observation indicators in this study. In addition, adverse reactions will be observed and recorded as safety indicators.

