Non-active thyroid associated ophthalmopathy is a refractory disease, which seriously affects the quality of life of patients. Currently, treatment means for non-active thyroid-related eye diseases are limited, and the curative effect is poor. Therefore, a treatment method with accurate curative effect and easy to be accepted by patients is urgently needed. In recent years, it has been found that traditional medicine has unique advantages in the treatment of this disease, which can significantly reduce local inflammation, improve visual acuity and reduce the protrusion degree and the TCM syndrome score, prevent the recurrence of the disease, and reduce the adverse reactions of Western medicine. The Pingmu Decoction is a Chinese medicine consisting of Radix Astragali(Huangqi), Herba Epimedii(Yinyanghuo), Miltiorrhiza (Danshen), Sinapis Alba (Baijiezi), Oldenlandia Diffusa (Baihuasheshecao), Semen Plantaginis (Cheqianzi), etc. It has beneficial temperature Yang, dispel phlegm stasis effect, and can effectively reduce the eyeball protrusion and TCM syndrome score in patients with non-active thyroid-related eye disease, which is characterized by deficiency of Yang qi and blockage of phlegm and blood stasis.^[6]^ According to [name],^[7]^ Pingmu Decoction can inhibit the accumulation of post-ocular adipose tissue in GO mice by inhibiting the proliferation activity of preadipocytes, reducing the differentiation of preadipocytes into adipocytes, and promoting the apoptosis of mature adipocytes after differentiation.^[8]^ It has been found in long-term clinical practice that Pingmu Decoction combined with acupuncture has a good effect on this disease, but there is still a lack of evidence to prove it. Therefore, we designed this prospective, randomized controlled clinical trial to further evaluate the efficacy and safety of Pingmu Decoction combined with acupuncture in the treatment of non-active thyroid-related eye disease, and to provide a new treatment regimen for non-active thyroid-related eye disease.

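### The trial is sized for a three-group ANOVA that does not by itself show the combination beats either component, and two primary outcomes are both judged at P < .05 without a stated joint rule

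*Protocol article*

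**What the plan says.** All places are in the protocol article.

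- **Outcomes.** The Abstract (Methods/Design) states: "The primary outcomes are to observe the degree of prominence of eyes, and the TCM syndrome scores". Section 2.7.1 lists the same two.
- **Arms.** Section 2.1 defines the "experimental group (Pingmu Decoction + acupuncture), control group 1 (Chinese medicine group) and control group 2 (acupuncture group"). All three arms keep basic western treatment; none receives it alone.
- **Aim.** The Introduction says the trial is designed "to further evaluate the efficacy and safety of Pingmu Decoction combined with acupuncture".
- **Tests.** In section 2.11, "ANOVA test will be used for comparison among three groups". The section also says "Continuous variables subject to normal distribution will be analyzed by Student" *t* test, with rank tests for non-normal data, but does not say what these compare. For the secondary outcome, "the comparison of effective rates between groups are performed by" a chi-square test. The threshold closing the section is P "< .05 will be considered statistically significant".
- **Sample size.** Section 2.4 works "according to the α = 0.05, β = 0.1", with a formula for k = 3 groups and ψ = 2.52, on exophthalmos reduction only. It obtains about 36 per arm, raised to 40 for 10% loss, 120 in total.

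**The concern.** The only comparators are the two components. The randomisation therefore informs about the combination through two contrasts: combination versus decoction and combination versus acupuncture. The plan names neither as decisive. The test it names and powers asks whether any of the three means differ. It can be significant because the two control arms differ from each other, or because the combination beats one component and not the other. A significant P value could then be reported as support for a combination that adds nothing to one of its parts.

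In addition, two outcomes are primary under one flat threshold, and the text does not say whether one or both must succeed. If either suffices, the chance of a false claim exceeds 5%. The stated 90% power covers only one of the two outcomes, and for that outcome only the omnibus test.

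**Working it through.** **1. Reproducing the plan's 36 per arm.** Inputs from section 2.4: α = 0.05, power 0.90, k = 3, ψ = 2.52, SD 1.3 mm, n = ψ²(Σσᵢ²/k) / [Σ(μᵢ−μ)²/(k−1)].

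- ψ is correct for an omnibus test: the noncentral chi-square with 2 df needs λ = 12.65, and √(12.65/2) = 2.515.
- The section prints 1.3 as the mean of every group, which makes the denominator zero. Separate group means must therefore be assumed.
- One arm δ better than two equal arms: Σ(μᵢ−μ)²/2 = δ²/3, so n = 3 × 2.52² × 1.3² / δ² = 32.2/δ². Setting n = 36 gives δ = √(32.2/36) = 0.946 mm. At δ = 1.0 mm, n = 32.2.
- Evenly spaced means with step g: Σ(μᵢ−μ)²/2 = g², so n = 10.73/g². Setting n = 36 gives g = 0.546 mm, a spread of 1.092 mm.
- Two other readings also give 36. One arm at 1.9 ± 1.1 and two at 1.0 ± 1.3 gives 6.35 × 1.53 / 0.27 = 35.99. A single two-sided two-group comparison at 1 mm, SD 1.3 and 90% power gives 35.5.
- 36/0.9 = 40, and 3 × 40 = 120.

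So 36 is reproducible, but only with means that the section does not print. The differences used below are assumptions, shown as a range.

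**2. What the omnibus test shows about the combination.** Simulation: 200,000 runs, 36 evaluable per arm, SD 1.3, pooled variance, two-sided 0.05. Means are mm of benefit in the order combination, decoction, acupuncture.

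| Means | ANOVA significant | Combination beats both |
|---|---|---|
| 0.946, 0, 0 | 89% | 78% |
| 1.0, 0, 0 | 92% | 83% |
| 1.092, 0.546, 0 | 89% | 42% |
| 0.946, 0.946, 0 | 89% | 2.5% |
| 0, 0.946, 0 | 89% | essentially never |

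In the fourth row acupuncture adds nothing to the decoction. In the fifth the combination is worse than the decoction and no better than acupuncture. The ANOVA is as likely to be significant in both as in the first row.

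**3. False-positive risk with no true difference.** If success on either primary counts and the two outcomes are independent, two omnibus tests give 1 − 0.95² = 9.75%. Simulated (100,000 runs) by correlation between the two outcomes:

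| Tests at 0.05 | 0 | 0.3 | 0.5 | 0.7 |
|---|---|---|---|---|
| Two omnibus ANOVAs | 9.7% | 9.5% | 9.2% | 8.6% |
| Combination vs each control, two outcomes | 17.4% | 17.0% | 16.1% | 15.0% |
| All three pairs, two outcomes | 23.0% | 22.4% | 21.3% | 19.7% |

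Only the first row follows from the test that section 2.11 names. The other two assume that the *t* or rank-sum tests are run pairwise without first requiring a significant ANOVA.

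**4. The both-contrasts rule.** With no true difference, the combination beats both controls in about 0.5% of trials. When it equals one component and is well ahead of the other, the false claim occurs in about 2.5% (fourth row of step 2). No alpha split is needed.

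**The case against.** Four points deserve weight.

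- **The analysis plan may settle this.** A condensed article with an unshown SAP may leave multiplicity detail there, and the closing threshold is a generic convention, not a success rule. This stands as far as the absence of a joint rule goes, and there is no inflation if both primaries must succeed. But the article itself fixes the omnibus basis of the sample size. A SAP rule requiring superiority over both components would still leave the 90% in section 2.4 attached to a different test.
- **Pairwise testing is inferred.** A reader might infer a false-positive risk of 20% or more as a property of the plan. Section 2.11 does not support that: its *t* and rank tests could be before-after comparisons within arms. If pairwise tests follow only a significant three-group ANOVA, the error stays near 5% per outcome, about 9.75% at most over two.
- **Each contrast is useful alone.** A reader might infer that superiority over both components is the only efficacy claim the randomisation allows. It is not. Combination versus acupuncture validly estimates what the decoction adds, and combination versus decoction what acupuncture adds. Beating both is needed only to claim that the combination is better than either. The article states its aim more loosely, as efficacy of the combination.
- **The trial is not grossly underpowered.** At 1 mm and SD 1.3, 36 per arm gives 90% power for one two-sided contrast and about 83% for both.

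**Conclusion.** The concern holds in this form. The named and powered test does not establish that the combination beats either component, and it can be significant with about 89% probability when the combination adds nothing to one of them. The stated 90% is omnibus power on exophthalmos. For beating both components it is about 78% at 0.946 mm and 83% at 1.0 mm if the control means are equal, falling to about 42% if the means are evenly spaced. All of these assume SD 1.3 mm, 36 evaluable per arm and differences that section 2.4 does not print; its 1 mm is a threshold for reduction, not a stated difference between arms.

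The false-positive risk is about 9-10% if success on either primary counts. It is 15-23% only if unguarded pairwise tests are used as well, which the text neither states nor rules out. No power is given for the TCM score.

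**What to change.** - **Section 2.11.** Make two contrasts decide: combination versus decoction and combination versus acupuncture, on change in exophthalmos at week 12, each at two-sided 0.05. Require both in order to claim that the combination is better than either component. Report the three-group ANOVA as supportive, and say what the *t* and rank tests compare.
- **Abstract and section 2.7.** State how the two primaries are judged. One option is to make the TCM score the first secondary outcome, since exophthalmos is already the sizing basis. The other is to keep both as primary and require both, in which case power for the TCM score must also be stated.
- **Section 2.4.** Say that the 90% refers to the omnibus test, print the assumed group means, and restate power for the both-contrasts rule under them. The 78%, 83% and 42% above should be quoted only with their assumptions.
- **Conclusions.** Limit them to benefit over, or added to, each component, because no arm receives basic treatment only.

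Cost: wording in the Abstract and sections 2.4, 2.7 and 2.11, and a lower stated power. No extra patients are needed if that power is accepted. Keeping 90% for both contrasts at 1 mm, SD 1.3 and equal control means would take about 43 evaluable per arm by normal approximation: 43/0.9 = 47.8, so 48 per arm and 144 in total.
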